## Abstract

Acupuncture is an alternative therapy to induce ovulation in women with polycystic ovary syndrome (PCOS), but there is no study reporting the live birth rate following ovulation induction by acupuncture or its potential as an adjuvant treatment to clomiphene citrate (CC). We assess the efficacy of acupuncture with or without CC in achieving live births among 1000 PCOS women in Mainland China. This paper reports the methodology of an ongoing multicenter randomized controlled trial. The randomization scheme is coordinated through the central mechanism and stratified by the participating sites. Participants will be randomized into one of the four treatment arms: (A) true acupuncture and CC, (B) control acupuncture and CC, (C) true acupuncture and placebo CC, and (D) control acupuncture and placebo CC. To ensure the quality and integrity of the trial we have developed a unique multinational team of investigators and Data and Safety Monitoring Board. Up to the end of April 2013, 326 subjects were recruited. In conclusion, the success of this trial will allow us to evaluate the additional benefit of acupuncture beyond the first line medicine for fertility treatment in PCOS women in an unbiased manner.

## 1. Introduction

Polycystic ovary syndrome (PCOS) is the most common endocrine disorder in women of reproductive age. It is characterized by ovulatory dysfunction, hyperandrogenism, and polycystic ovaries (PCO) and affects 5–10% of premenopausal women [1]. In addition to irregular menses, hirsutism, and infertility, women with PCOS may display a number of metabolic abnormalities including hyperinsulinemia, insulin resistance, dyslipidemia, and obesity [2]. Clomiphene citrate (CC) is considered as the first line treatment to induce ovulation in women with PCOS. A compilation of published results from 5,268 patients revealed an ovulation rate of 73% per cycle per patient, pregnancy rate of 36% per patient, and live birth rate of 29% per patient during a six-month treatment [3]. Women who do not ovulate while receiving the maximum 150 mg dose are considered to be CC resistant and those who do not conceive after an ovulatory response are considered clomiphene failures. Both appear to be common [4], necessitating the search for adjuvant therapies to treat infertility in women with PCOS. 

Inability of CC to induce ovulation is more likely in patients who are obese, insulin resistant, and hyperandrogenic compared with those who do respond [5]. The mechanism of CC failures may partly be explained by a peripheral anti-estrogenic effect at the level of endometrium and cervical mucus or by hypersecretion of luteinizing hormone (LH). Side effects of CC are related to its combined estrogenic and antiestrogenic properties, which include hot flushes, breast discomfort, abdominal distension, nausea, vomiting, nervousness, sleeplessness, headache, mood swings, dizziness, hair loss, and disturbed vision [4]. Approximately 7% of pregnancies resulting from CC-induced ovulation are twin pregnancies and 0.5% are triplet pregnancies [6]. 

The choice of adjuvant treatments or second line treatment is controversial. The benefit of combined metformin/CC has been called into question by the meta-analysis [7]. Gonadotropin treatment can be offered as the second line drug when anovulatory PCOS women fail to respond to CC. The use of gonadotropin is more expensive than CC and associated with a higher risk of multiple pregnancies and development of ovarian hyperstimulation syndrome. Ovarian drilling by diathermy or other methods is the second line therapy with equal efficacy to gonadotropin [8]. However this treatment is also expensive and invasive. New or additional treatments that are readily accessible, affordable, and safe are needed.

Acupuncture is an integral part of Traditional Chinese Medicine (TCM), which dates back to more than 3,000 years. In recent years, the use of acupuncture within reproductive endocrinology and infertility has gained increased popularity worldwide [9–11]. From a physiological perspective, the effect of acupuncture is most likely mediated via activation of sensory nerve fibers, which in turn modulate the sympathetic activity to the ovaries and from the central nervous system (CNS). Support for the theory that acupuncture, at least in part, modulates sympathetic activity arises from the findings that acupuncture decreases high ovarian expression of sympathetic markers and increases ovarian blood flow, an effect mediated as a reflex response via ovarian sympathetic nerves and via CNS [12–14]. Further, both acupuncture and exercise reduced high muscle sympathetic nerve activity in women with PCOS [15, 16].

In PCOS women with ovulatory dysfunction, several nonrandomized trials revealed that repeated acupuncture treatments decreased total testosterone and other sex steroid levels, reduced LH/follicle-stimulating hormone (FSH) ratio, and improved menstrual frequency without negative side effects [17–19]. In a randomized controlled trial (RCT), fourteen acupuncture treatments, with combined electrical and manual stimulation of the needles during 16 weeks and 16 weeks of physical exercise compared with no intervention, improved menstrual bleeding pattern and decreased high levels of sex steroid precursors, estrogens, androgens, and glucuronidate androgen metabolites in women with PCOS [20]. Acupuncture was superior to physical exercise when compared directly after the treatment period. In a quasi-randomized study, daily abdominal acupuncture during 6 months improved menstrual frequency and decreased circulating testosterone more effectively than metformin during 6 months [21]. Recently in another RCT, 12 treatments of true acupuncture were compared with control acupuncture using placebo needles during 8 weeks and similar ovulation rates were found in both groups of women with PCOS [22]. 

Findings from previous clinical and experimental studies indicate that acupuncture may induce ovulation and improve pregnancy in women with PCOS. However, the methodological quality of these studies is of varying quality, and none were designed to investigate pregnancy or more importantly live birth. We sought to address these gaps in knowledge by designing an RCT to examine the effects of acupuncture on live birth in women with PCOS. The objective of the present trial is to test the following three hypotheses in anovulatory women with PCOS: (1) true acupuncture and CC are more likely to result in live birth than control acupuncture and CC, (2) control acupuncture and CC are more likely to result in live birth than true acupuncture and placebo CC, and (3) true acupuncture and placebo are more likely to result in live birth than control acupuncture and placebo CC.

## 2. Materials and Methods

### 2.1. Study Population

Subjects will be recruited from 25 hospitals across 13 provinces in Mainland China when they seek treatments for ovulatory problems and pregnancies. They will be eligible if they meet the following inclusion and exclusion criteria. Informed consent will be obtained after detailed explanation, and each will be given a copy of the signed consent.

Inclusion criteria are as follows. Age of women between 20 and 40 years.Chronic oligomenorrhea or amenorrhea: oligomenorrhea is defined as an intermenstrual interval >35 days or <8 menstrual bleedings in the past year. Amenorrhea is defined as an intermenstrual interval >90 days. Hyperandrogenism (either hirsutism or hyperandrogenemia) or polycystic ovaries on ultrasound. Hirsutism is determined by a modified Ferriman-Gallwey Score ≥ 5 at screening examination [23]. Polycystic ovaries are present when there are ≥12 antral follicles (2–9 mm) or ovarian volume >10 mL on transvaginal scanning [24].Further, at least one patent tube and normal uterine cavity shown by hysterosalpingogram, HyCoSy, or diagnostic laparoscopy with chromotubation within three years [25].Sperm concentration ⩾15 × 10^6^/mL and total motility ⩾ 40% or total motile sperm count ⩾  10 million in the semen analysis of the husband [26, 27].Agree to have regular intercourse, that is, 2-3 times per week during the study period.

Exclusion criteria are as follows. Exclusion of other endocrine disorders: *①* patients with hyperprolactinemia ( defined as two prolactin levels at least one week apart ⩾25 ng/mL) *②* Patients with FSH levels > 15 mIU/mL. A normal level within the last year is adequate for entry. *③* Patients with uncorrected thyroid disease (defined as TSH <0.2 mIU/mL or >5.5 mIU/mL). A normal level within the last year is adequate for entry. *④* Patients diagnosed with Type I or Type II diabetes who are poorly controlled (defined as HbA1c level > 7.0%), or patients receiving antidiabetic medications such as metformin, insulin, thiazolidinediones, acarbose, or sulfonylureas. *⑤* Patients with suspected Cushing's syndrome.Use of hormonal or other medication including Chinese herbal prescriptions in the past 3 months.Pregnancy within the past 6 weeks.Within 6 weeks postabortion or postpartum.Breastfeeding within the last 6 months.Not willing to give written consent to the study. Additional exclusion criteria are as follows.
Patients on oral contraceptives, depot progestins, or hormonal implants (including Implanon). A two-month washout period will be required prior to screening for patients on these agents. Longer washouts may be necessary for certain depot contraceptive forms or implants, especially where the implants are still in place. A one-month washout will be required for patients on oral cyclic progestins. Patients with liver disease defined as AST or ALT > 2 times normal or total bilirubin > 2.5 mg/dL. Patients with renal disease defined as BUN > 30 mg/dL or serum creatinine > 1.4 mg/dL.Patients with hemoglobin < 10 g/dL.Patients with a history of deep venous thrombosis, pulmonary embolus, or cerebrovascular accident.Patients with known heart disease that is likely to be exacerbated by pregnancy.Patients with a history of, or suspected cervical carcinoma, endometrial carcinoma, or breast carcinoma. A normal Pap smear result will be required for women 21 and over.Patients with a current history of alcohol abuse. Alcohol abuse is defined as >14 drinks/week or binge drinking. Patients enrolled into other investigative studies that require medications, prescribe the study medications, limit intercourse, or otherwise prevent compliance with the protocol. Patients who anticipate taking longer than a one-month break during the protocol should not be enrolled. Patients taking other medications known to affect reproductive function or metabolism. These medications include oral contraceptives, GnRH agonists and antagonists, antiandrogens, gonadotropins, antiobesity drugs, Chinese herbal formula, antidiabeteic drugs such as metformin and thiazolidinediones, somatostatin, diazoxide, angiotensin-converting-enzyme (ACE) inhibitors, and calcium channel blockers. The washout period on all these medications will be two months.Patients with a suspected adrenal or ovarian tumor secreting androgens.Couples with previous sterilization procedures (vasectomy, tubal ligation), which have been reversed. The prior procedure may affect study outcomes, and patients with both a reversed sterilization procedure and PCOS are rare enough that exclusion should not adversely affect recruitment. Subjects who have undergone a bariatric surgery procedure in the recent past (<12 months) and are in a period of acute weight loss or have been advised against pregnancy by their bariatric surgeon.Patients with untreated poorly controlled hypertension defined as a systolic blood pressure 160 mm Hg or a diastolic 100 mm Hg obtained on two measures obtained at least 60 minutes apart.Patients with known congenital adrenal hyperplasia.

### 2.2. Study Design

This is a multicenter, randomized, double-blinded, controlled, 2 by 2 factorial clinical trial for PCOS women in China, with study treatment during 4-month cycles. Participants are randomized to receive either an initial oral dose of 50 mg of CC or placebo CC from day 3 to day 7 of the cycle [4] in combination with one of the two acupuncture procedures. The starting date for CC is not expected to affect the treatment outcome [28]. In order to maintain the double-blinding for the medication, CC and placebo CC were packaged in identically appearing numbered study kits which were then directly shipped to each clinical site. For acupuncture, all patients will receive either true or control acupuncture treatment. 

### 2.3. Randomization

Randomization takes place as soon as the eligibility requirements are met. Participants are randomized into one of the four treatment arms: (1) true acupuncture and CC, (2) control acupuncture and CC, (3) true acupuncture and placebo CC, and (4) control acupuncture and placebo CC by an interactive online computer program in a central office. Using a 1 : 1 : 1 : 1 treatment ratio, there will be 250 women assigned to each treatment group and we expect the dropout rate would be 20%. The randomization is stratified within each of the participating sites by a random block algorithm. The data coordinating center (DCC) statisticians generated and validated the randomization scheme for the study before it was implemented in a web-based database system, and the study coordinator at each participating site logs on the web-based system to retrieve the randomization number after a patient is ready for it. The CC and placebo CC assignments are double-blinded, unknown to patients and study investigators except the DCC data manager. The true and control acupuncture treatments are known only to the TCM specialist (besides the DCC data manager) of the participating site that performs the randomized procedure. 

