### 2.11. Sample Size Calculations

The overall live birth rate for women to receive CC is estimated to be 20% during the 4-month period according to Chinese Obstetrics and Gynecology (Second Edition). Due to lack of existing data on the effectiveness of acupuncture, we cannot rely on the literature for samples size determination. Instead we hypothesize that the order of effectiveness of the treatments is as follows: True acupuncture and CC > Control acupuncture and CC,  control acupuncture and CC > True acupuncture and placebo CC,  true acupuncture and placebo CC > Control acupuncture and placebo CC. The respective live birth rates are projected with 10% difference as follows and the average rate among four arms is 15% (Table 3).

 Using a two-sided trend test and with an effective sample of 200 per group, our study is designed to have >80% power at the significance level of 0.015 (we have three primary hypotheses). The sample size has been inflated from 200 to 250/arm to allow for a dropout rate of 20%, totally 1000 cases for four arms. 

There have been multiple trials to study the effects of CC in PCOS women. The primary aim of this trial is not to reassess the efficacy of CC. The aim is to elucidate the additional efficacy of acupuncture in combination with CC, or acupuncture alone. Acupuncture is compared with CC because CC has been demonstrated to be superior to metformin [4]. The previous study design is used as a role model since it was the best executed and most cited trials in this area. [name] chairs the Steering Committee of this trial, and [name] leads the DCC for another trial using CC in PCOS women. They have considered all related studies, although the power calculation involved inevitably some assumptions. The significance level of 0.015 is approximately 0.05/3 because in this study the overall significance level is controlled to 0.05 after correcting for the multiple comparisons involving three primary hypotheses.

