### 2.12. Data Analysis

The primary outcome is the live birth rate. Secondary outcomes include (1) ovulation rate; (2) ongoing pregnancy rate at gestation 8–10 weeks; (3) multiple pregnancy rate; (4) miscarriage rate: loss of an intrauterine pregnancy before 20 completed weeks of gestation; (5) change in hormonal profile: FSH, LH, T, SHBG, and DHEAS; (6) change in metabolic profile: glucose and insulin concentrations, cholesterol, triglycerides, HDL-C, and LDL-C; (7) side effect profile; (8) change in QOL; (9) change in symptoms of anxiety and depression; and (10) credibility assessments.

The analysis will use an intent-to-treat (ITT) approach to examining differences in the live birth rates among the four treatment arms. Primary efficacy analysis will be done by comparing the treatment groups with respect to the primary outcome of live birth using the Pearson Chi-square test. For the secondary, supportive analysis, we will fit a logistic regression model to compare the treatment arms with respect to the primary outcome of live birth, adjusting for other factors such as randomization stratification of study site and prior exposure to study medications. The analysis of other secondary outcomes measured over time will entail the application of statistical methods that have been developed for correlated data since repeated observations will be made over time on each individual. For secondary outcomes such as hormone levels, a linear mixed-effects model will be fit where the main independent variables will be treatment group, time, and their interaction as well as the designed randomization stratification factors as covariates. Logistic regression models will be used in secondary analyses to evaluate the predictive value of treatment arm, clinical site, prior exposure to CC, body mass index, and other explanatory variables on binary outcomes (e.g., singleton live birth, abortion). Cox proportional hazards models and a Kaplan-Meier method will be applied to compare time to pregnancy in the treatment groups. 

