### 3.3. Study Progress and Recruitment

The targeted duration of recruitment will be 18 months and 25 hospitals at 21 sites are involved. In order to achieve our enrollment goal of 1,000 randomized subjects, each site must contribute 40–50 subjects, which amounts to about one recruited subject per site per week. There are a four-month treatment period and another nine-month period to follow up the pregnancy outcome. Therefore from the initial recruitment to the completion of the follow-up, a total of 31 months (2.5 years) will be required to complete the study. Up to the end of April 2013, 326 subjects were recruited.

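### Randomisation is stratified by site but the primary live-birth test ignores site, so the test is somewhat conservative if sites differ

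*Protocol article*

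**What the plan says.** On allocation, section 2.3 states: "The randomization is stratified within each of the participating sites by a random block algorithm". The abstract also says that randomisation is stratified by participating site. Section 3.3 gives the number of strata: "25 hospitals at 21 sites are involved".

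On analysis, section 2.12 defines the primary efficacy analysis as "comparing the treatment groups with respect to the primary outcome of live birth using the Pearson Chi-square test". It names no stratification factor for this test. Site comes in one step lower: "For the secondary, supportive analysis, we will fit a logistic regression model to compare the treatment arms", and that model works by "adjusting for other factors such as randomization stratification of study site and prior exposure to study medications". For hormone levels and similar outcomes, the same section fits linear mixed models with the randomisation stratification factors as covariates.

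On size, section 2.11 says "Using a two-sided trend test and with an effective sample of 200 per group" and "our study is designed to have >80% power at the significance level of 0.015". The 0.015 is a share of 0.05 across three primary hypotheses, each of which compares two arms.

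**The concern.** Blocking within site holds the arms in near-equal numbers at every site, so differences in live birth between sites largely cancel out of the treatment contrast. The unstratified chi-square does not use this. Its variance comes from the pooled birth rate and still contains the between-site spread. When sites differ, the standard error is too large, the p-value is too large on average, and the test rejects less often than its stated level.

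The article gives some reason to expect site differences. The hospitals span 13 provinces (section 2.1), and section 2.10's counterpart on treatment, section 2.4, accepts that the acupuncturist's training and experience may affect outcome.

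The plan is also uneven by its own standard: the analysis follows the randomisation for secondary outcomes but not for the outcome that decides the trial. What is at stake is some efficiency on the primary comparisons, not the validity of a positive result.

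**Working it through.** **Inputs.** Rates of 25, 15, 15 and 5% in arms A to D (Table 3); 200 evaluable and 250 randomised per arm; two-sided alpha 0.015, so critical z = 2.4324; 21 sites. Assumed: near-equal sites, 1:1 balance within site, a normal site effect on the logit scale, and the chi-square applied to each pair of arms. The documents do not give the site SD, so it is varied from 0 to 1.0. For a mean rate of 15%, the central 90% of sites would lie at roughly 7 to 27% with SD 0.5 and 4 to 35% with SD 0.8.

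**1. The plan's own figures.** Trend test, centred scores 1.5, 0.5, −0.5, −1.5:
- Contrast = 1.5×0.25 + 0.5×0.15 − 0.5×0.15 − 1.5×0.05 = 0.30
- Null SE = √(0.15×0.85×5/200) = 0.0565; SE under the alternative = √(0.5925/200) = 0.0544
- Power = Φ[(0.30 − 2.4324×0.0565)/0.0544] ≈ 99.9%, which satisfies the stated >80%
- Dropout: 200/(1 − 0.20) = 250

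This power is for a trend test. The pairwise A-versus-B comparison, without site effects, has Φ[(0.10 − 2.4324×0.0400)/0.0397] = 52.7%.

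**2. Why the test is conservative.** Let p_s be the rate at site s and p̄ the mean rate. With n women per arm, under the null:
- Variance assumed by Pearson: p̄(1 − p̄)·2/n
- Actual variance under within-site balance: [p̄(1 − p̄) − Var(p_s)]·2/n

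The effective critical value is therefore 2.4324/√r, with r = 1 − Var(p_s)/[p̄(1 − p̄)]. For p̄ = 0.15, p̄(1 − p̄) = 0.1275.

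| Site SD (logit) | SD of site rates | r | Effective z | Implied type I error |
|---|---|---|---|---|
| 0.3 | 0.0367 | 0.989 | 2.445 | 0.0145 |
| 0.5 | 0.0606 | 0.971 | 2.468 | 0.0136 |
| 0.8 | 0.0945 | 0.930 | 2.522 | 0.0117 |
| 1.0 | 0.1150 | 0.896 | 2.569 | 0.0102 |

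**3. Simulation.** 20,000 trials per setting, 200 per arm. The CMH statistic sums over sites the births in one arm minus m/2, and divides by the root of the summed variances n²m(T − m)/[T²(T − 1)], where n is women per arm at the site, T = 2n, and m is the site's births in both arms.

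| Site SD | Type I error, Pearson / CMH | A vs B power, Pearson / CMH | C vs D power, Pearson / CMH |
|---|---|---|---|
| 0 | 0.0142 / 0.0146 | 53.5% / 52.9% | 84.0% / 84.0% |
| 0.3 | 0.0149 / 0.0155 | 53.6% / 53.8% | 83.8% / 84.0% |
| 0.5 | 0.0128 / 0.0140 | 53.2% / 54.5% | 83.9% / 84.6% |
| 0.8 | 0.0112 / 0.0146 | 52.8% / 56.6% | 84.3% / 85.9% |
| 1.0 | 0.0101 / 0.0155 | 53.4% / 59.8% | 84.0% / 86.3% |

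The Monte Carlo standard error of the type I errors is about 0.0009. A separate run gave Pearson 0.0125 against CMH 0.0142 at SD 0.5, and 0.0106 against 0.0139 at SD 0.8. Its A-versus-B power gains were about 0 points up to SD 0.3, then 1.4, 4.0 and 6.2 points at SD 0.5, 0.8 and 1.0. The two runs and the formula agree within simulation error.

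For B versus C, Table 3 projects 15% in both arms, so no power loss can be computed from the plan's rates.

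**The case against.** The strongest defence is that the unstratified chi-square is a valid and transparent primary test, that site adjustment of live birth is already planned, and that the loss rests on a site variation found nowhere in the article. All three points stand. At SD 0 nothing is lost, at SD 0.5 the loss is 1 to 1.5 points, and a loss of 4 points needs site rates spread about ninefold.

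A reader might infer four stronger things, which the article does not support:

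- **That the primary result could be a false positive because site is ignored.** The error runs the other way: actual type I error is at or below 0.015.
- **That the planned site-adjusted logistic model is too sparse to rely on.** Site effects are estimated from all four arms. At about 12 women per arm per site, a site expects 12 × (0.25 + 0.15 + 0.15 + 0.05) = 7.2 births. In simulation at that size the model converged in at least 99.98% of runs and tracked CMH: at SD 0.8, A-versus-B power was 65.6% for Pearson, 69.8% for CMH and 70.5% for logistic.
- **That an adjusted and an unadjusted result leave open which one counts.** Section 2.12 ranks them as primary and supportive.
- **That site stands in for the acupuncturist.** With 35 trained acupuncturists at 21 sites there are about 35/21 = 1.7 per site, so the match is only partial.

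The analysis plan is not shown and may say more. But the article itself names the primary test and gives the site-adjusted analysis a lower rank, so the choice can be judged as written.

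**Conclusion.** The point holds as a modest one about efficiency and about matching the analysis to the design. The primary test leaves out the factor used to stratify randomisation, while the secondary mixed models include it. At 200 per arm, actual type I error falls from the nominal 0.015 to 0.0125–0.0128 at site SD 0.5 and 0.0106–0.0112 at SD 0.8. The A-versus-B power lost is about 0 points at SD up to 0.3, 1.4 at 0.5, 4 at 0.8 and 6 at 1.0. For C versus D it is smaller, about 2 points at SD 1.0.

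These figures rest on an assumed site SD, 21 near-equal sites, the rates in Table 3 and pairwise testing at 0.015. Stratifying does not repair the low A-versus-B power: about 53% becomes 54.5% at SD 0.5. That shortfall is a separate matter.

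**What to change.** In section 2.12, for each of the three pairwise hypotheses, make the primary test a Cochran-Mantel-Haenszel test stratified by site, reported with a Mantel-Haenszel risk difference and confidence interval. Set in advance a rule for pooling very small sites. Promoting the planned site-adjusted logistic model to primary would serve equally well. Keep the unstratified Pearson chi-square as a sensitivity analysis.

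The cost is wording only, since site is the randomisation stratum and is already recorded. If sites turn out not to differ, the price is at most about half a point of power (53.5% to 52.9% for A versus B). The article reports 326 of 1,000 women recruited and, apart from medical emergencies, delays unblinding until final outcomes are in, so the change could be made before any unblinded comparison.
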